### 3.6.3 Drugs supplying

The first drug supply will be estimated for consumption based on the previous research work, and mailed to all clinical study centers. If the drugs are used with residual 1/4 in the study center, they should timely contact with the unit in charge, to determine the need for replacement drugs according to the study schedule.

### 3.6.4 Study finished

Each clinical research center will return the remaining drug to the sponsor.

# Auxiliary examination

## **4.1 Dynamic outcomes**

### 4.1.1 Detection outcomes

（1）安全性指标：血、尿、便常规，心电图，ALT、AST、BUN、Cr

(1) safety outcomes: blood, urine, stool routine, electrocardiogram, ALT, AST, BUN, Cr（2）疗效性指标：NEI网络指标（促肾上腺皮质激素、血浆皮质醇、生长激素、雌二醇、睾酮、儿茶酚胺、乙酰胆碱、血管活性肠肽、促甲状腺素；CD3+、CD4+、CD8+细胞比例，CD4+/CD8+之比；IL-2、IFNγ、TGF、IL-1），T-tau、P-tau、Aβ1-42

(2) outcomes of curative effect: NEI network index (adrenocorticotropic hormone, cortisol, growth hormone, estradiol, testosterone, catecholamine, acetylcholine, vasoactive intestinal peptide, thyroid stimulating hormone; CD3+, CD4+, CD8+ , CD4+/CD8+ ; IL-2, IFNγ, TGF, IL-1), T-tau, P-tau,Aβ1-42

### 4.1.2 Sampling point（1）安全性指标：入组（0天）、治疗后12周、治疗24周后

(1) safety indicators: baseline (0 week), week 12(treatment), week 24(treatment);（2）疗效性指标：NEI网络指标：入组（0天）、治疗4周后、治疗24周后

(2) outcomes of curative effect:

NEI: baseline (0 week), week 4(treatment), week

24(treatment);T-tau、P-tau、Aβ1-42：入组（0天）、治疗24周后

T-tau, P-tau, Aβ1-42: baseline (0 week), week 24(treatment);

### Related materials

（1）安全性指标各中心按要求分别完成，常规取血检测。

(1) Safety outcomes should be performed in each center.

（2）疗效性指标由上海中医药大学附属龙华医院承担。

(2) Index of curative effect should be performed by Longhua hospital affiliated to Shanghai University of TCM.

## **4.2 BOLD-fMRI, magnetic resonance spectroscopy, hippocampus formation**

### 4.2.1 Performed

In the Second Affiliated Hospital of Tianjin University of TCM.

### 4.2.2 Data saving

The images are saved as photos, papers, and discs.

### 4.2.3 Operation

**(1) Image acquiring**

MRI data were acquired on a Siemens Trio scanner (SiemensMedical Systems, Erlangen, Germany) at 3 T, using a standard orthogonal coil.

Acquisition sequence: T1WI, T2WI, FLAIR image: used to exclude organic disease, cerebrovascular disease, using clinical scanning routine sequence, without defined scanning parameters.

Anatomical study: in a 3D gradient recalled echo T1 weighted image, sagittal images, 176 layer, TR/TE=1900/2.5ms, 9 degrees flip angle, slice thickness 1.0mm,FOV=250mm * 250mm, matrix =256 * 256.

Brain functional images: EPI series, TR/TE= 3000/30ms, 90 degree flip angle, slice  thickness 4.0mm, 1.0mm interval, a total of 25 layers, FOV=220mm * 220mm, matrix =64 * 64 , with the scanning time of 12min. The scanning range is parallel to the posterior, collecting a total of 240 time points.

Hippocampal volume measurement: the anatomical image 3-D data is performed to outline and segment the hippocampus, calculate cingulate cortex, cortex of temporal lobe, and temporal lobe single voxel. MRS measurements: TR: 2000ms, TE: 30ms, 2048 data points; stimulation: 128 times, the volume of interest: 8cm3 (2 * 2 * 2cm).

**(2) Functional brain imaging stimulus**

The stimulus is designed by E-PRIME. The patient will be trained before scanning, and the synchronous trigger brain functional imaging task presentation system is performed to present the stimuli. The patients watch the image presented on the screen through the standard reflector fixed above the orthogonal coil, and the image is 0.6 meter away from the patients. During the scanning, the head should be fixed to reduce the influence of non-independent movement. Scanning plane is parallel to anterior skull base, namely the anterior commissure and the posterior commissure are in a line. The eyes and supratentorial structure is not on the same level to avoiding the influence of involuntary eye movement on the activation signal of the brain.

We use reformed adopted block stimulus plan, a repeated baseline to task (a block) pattern. There are 6 blocks, including a baseline of 20 frame images and task 20 frame images each, three seconds per frame of the image acquisition time, two minutes a group 12 minutes in total. The stimulus for the content is Chinese Stroop task, which includes three blocks for the congruent color words ( the word red printed in red,  word blue printed in blue,  word green printed green) task, three blocks for word and color in conflict (word green printed in red, printed red in blue, word blue printed in green). Three blocks of words and color in conflict is pseudo-randomized into blocks for the congruent color words, and vice versa. The data can be analyzed using a block design, also using event related design. Regarding the less pseudo random into conflict task, we use block designe.

**(3) Data analysis**

Data analysis is carried out using brain imaging Statistical Parametric Mapping 5.0(SPM 5.0) based on matlab 7.1. The scanning image is derived for the dicom image and converted to nifti format time correction by mricron; adjust the time point according to the scan acquisition mode; estimate the head movement parameters according to the position change information between the image acquisition frame; re-sample image registration according to the head movement parameters. Imaging registration is carried by mutual information of the low resolution functional  data and high-resolution anatomical image data; resample spatial standardization of the anatomic imaging data is carried in accordance with the function of spatial information: to estimate the deformed information during the spatial standardization according to the anatomy of the data after image registration; to carry the spatial standardization imaging smoothing of  anatomical images and function image after registration according to the information of deformation. 5mm Gauss smoothing necleus is used to convolution operate the functions imaging data after standardization, reduce the image noise, and improve data normality. According to stimulus presentation scheme, input the test design scheme in a statistical process, and the corresponding function data, to get the activation map image. Single factor variance analysis method is used to compare the differences of the brain function activation between two groups; paired t test, is used to test the situation changes of brain function before and after medication; independent sample t test is used to test the difference of brain activation changes in AD patients before and after medication, and comparing to the clinical data, cognitive test scores, single voxel MRS measurement of metabolic information to derive 3D map of the activated voxel coordinate, voxel number and intensity of activation information. Metabolite MRS (including NAA (2 ppm), Cr (3 ppm), Cho(3.2 ppm) and MI (3.56 ppm))  information is obtained according to the activated voxels of the map and the between group differences in body space positioning information of paired t test  to calculate MI/Cr NAA/Cr, Cho/Cr, and MI/NAA. According to the normality of the data, single factor analysis of variance or a plurality of groups of independent samples rank sum test parameter test can be used.

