## **3.5 Time point**

(1) Cognitive scales: baseline (0 week), week 12(treatment), week 24(treatment), week -48(follow up);

(2) Imaging (BOLD-fMRI, magnetic resonance spectroscopy, hippocampus formation): baseline (0 week), week 12(treatment);

(3) NEI network: baseline (0 week), week 4(treatment), week 24(treatment);

(4) Safety outcomes: baseline (0 week), week 12(treatment), week 24(treatment)**;**

(5) Specific parameters related to AD: baseline (0 week), week 12(treatment).

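### The spectroscopy location is tied to activation and group-difference maps, which conflicts with a single voxel placed at scanning, and the named imaging comparisons do not adjust for the baseline scan.

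*Protocol*

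**What the plan says.** **Where metabolites are read.** Protocol 4.2.3(3), Data analysis, says metabolite "information is obtained according to the activated voxels of the map and the between group differences in body space positioning information". The words that follow attach this positioning information to a paired t test. The section then forms MI/Cr, NAA/Cr, Cho/Cr and MI/NAA and says that, depending on normality, "single factor analysis of variance or a plurality of groups of independent samples rank sum test parameter test can be used".

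**How the voxel is acquired.** Protocol 4.2.3(1), Image acquiring, gives "the volume of interest: 8cm3 (2 * 2 * 2cm") as the spectroscopy volume. The sentence just before it, which is about measuring the hippocampus, ends with "calculate cingulate cortex, cortex of temporal lobe, and temporal lobe single voxel". The wording is garbled but names anatomical sites.

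**How activation is compared.** Protocol 4.2.3(3) lists three tests:
- "Single factor variance analysis method is used to compare the differences of the brain function activation between two groups";
- a within-patient comparison of pre-treatment and on-treatment activation, by a paired t test;
- a comparison of change, worded as "independent sample t test is used to test the difference of brain activation changes in AD patients before and after medication".

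Protocol 3.5 puts imaging at baseline and week 12. No baseline covariate is named for any imaging test. For the metabolite ratios, the text does not say whether a level or a change is analysed.

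**The concern.** There are two separate issues.

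First, if a location is picked because the arms differ there in activation, and the same patients' arms are then compared there on metabolites, the second test may inherit part of the chance difference that drove the choice. Its p-value would then not have its nominal meaning. The rule also looks unworkable: single-voxel spectroscopy gives data only where the voxel was placed, and a between-group map cannot guide the scans from which it is made.

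Second, each imaged patient is to have a baseline scan, yet none of the named comparisons between arms uses it as a covariate. What is at stake is precision. The number imaged is not stated, but imaging is done at one site (Protocol 4.2.1), which recruits 40 of the 120 patients (Protocol 3.2), so the imaging sample may be small.

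**Working it through.** The protocol gives no alpha, power, effect size or SD for imaging, so there is no stated figure to reproduce. The check has three parts.

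**1. The two placement rules side by side.**
- 4.2.3(1): one 2 x 2 x 2 cm = 8 cm3 volume, with cingulate and temporal sites named. Its position is set at acquisition.
- 4.2.3(3): position taken from activated voxels and between-group differences. Such a map exists only after patients in both arms have been scanned and processed.

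The second rule cannot set the voxel position in the scans that produce the map. This conflict needs no numerical assumption.

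**2. Size of the selection effect, if the map is a between-group one.**
Model under no treatment effect:
- K independent candidate regions;
- the region with the largest absolute activation contrast between arms is chosen;
- the metabolite contrast in that region is tested at two-sided 5%;
- rho is the correlation between the activation and metabolite contrasts in the same region.

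With Z the selected activation contrast, the metabolite contrast is rho x Z + sqrt(1 - rho^2) x e, with e standard normal. K and rho are assumptions. Simulated error rates (100,000 runs or more per cell):

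| K | rho = 0 | rho = 0.3 | rho = 0.5 |
|---|---|---|---|
| 1 (fixed voxel) | 5% | 5% | 5% |
| 2 | 5% | 5.6-5.7% | 6.7-6.8% |
| 3 | 5% | 6.0-6.1% | 7.9-8.0% |
| 10 | 5% | 8% | 13% |
| 50 | 5% | 11% | 21% |

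The rows for 2 and 3 regions are the relevant ones, because a single-voxel acquisition with a few named sites would not supply metabolite values for 10 or 50 regions.

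**3. Precision lost without baseline adjustment.**
Let r be the correlation of a measure between baseline and week 12 (assumed), with equal variances SD^2 at both times. Variance of the comparison relative to SD^2:
- follow-up only: 1
- change score: 2(1 - r)
- ANCOVA: 1 - r^2

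So ANCOVA / change = (1 - r^2) / [2(1 - r)] = (1 + r)/2, and ANCOVA / follow-up only = 1 - r^2.

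| r | ANCOVA / change | ANCOVA / follow-up only |
|---|---|---|
| 0.5 | 0.75 | 0.75 |
| 0.7 | 0.85 | 0.51 |

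Illustration in power, for an assumed effect of 0.5 SD, r = 0.7 and 40/2 = 20 per arm (imaging centre only). Power = Phi(0.5 / (s x sqrt(2/20)) - 1.96), with sqrt(2/20) = 0.316:
- follow-up only, s = 1: Phi(-0.38) = 35%
- change, s = sqrt(0.6) = 0.775: Phi(0.08) = 53%
- ANCOVA, s = sqrt(0.51) = 0.714: Phi(0.25) = 60%

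If all 120 patients were imaged (60 per arm), the same three figures are 78%, 94% and 97%.

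**The case against.** **The map may not be between-group.** The location sentence ends in a paired t test, which is a within-patient test. If the map is the before-after change pooled over both arms and made blind to group, the location is not chosen on the treatment contrast and the selection problem disappears. This stands: the text supports two readings. But the sentence also names between-group differences, and the ambiguity itself needs resolving.

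**The inflation is mostly assumed.** This stands too. The selecting measure (activation) differs from the tested one (metabolite ratio), so there is no inflation without correlation. A reader might infer error rates of 8-21%, but these need 10-50 candidate regions, and nothing in the protocol provides them.

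**The baseline scan is used.** A reader might infer that the imaging comparisons ignore baseline. They do not all do so: the independent t test on before-after change uses it. Nor does the protocol say that the ANOVA is on follow-up values only, so the 0.51 ratio is conditional on that reading.

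**Covariates may be left to the analysis plan.** In general they may. Here, though, the protocol itself names the tests, and neither test for comparing activation between arms is baseline-adjusted.

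**The acquisition text is too garbled to prove fixed volumes.** This is fair. The anatomical sites appear in a sentence on the hippocampus, so the volumes have to be defined explicitly and cannot simply be cited.

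**Conclusion.** The point holds in a limited form.

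- **Placement conflict:** firm. Sections 4.2.3(1) and 4.2.3(3) cannot both decide where metabolites are measured, and they must be reconciled.
- **Dependence of the metabolite test on the location choice:** conditional on a between-group map and on correlation between activation and metabolites. The size is nil at zero correlation and about 6-8% for a nominal 5% with 2-3 candidate regions and an assumed correlation of 0.3-0.5.
- **No baseline adjustment:** a loss of precision. A reader might infer that the treatment comparison is biased, but in a randomised comparison both the change-score and the follow-up-only tests are unbiased. ANCOVA variance is 0.75-0.85 of the change-score variance at an assumed r of 0.5-0.7, and 0.75-0.51 of a follow-up-only test if that is what the ANOVA is.

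The protocol does not name the metabolite ratios as a primary outcome, so this does not threaten the trial's main conclusion. It is worth correcting because the change is cheap.

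**What to change.** 1. Reconcile 4.2.3(1) and 4.2.3(3). State the anatomical spectroscopy volumes explicitly, set before scanning and the same for all patients and both visits. Delete the choice of location based on group differences.
2. Compare arms on week-12 regional activation and on week-12 metabolite ratios by ANCOVA, with the baseline value of the same measure as covariate. Add centre only if patients from more than one centre are imaged.
3. Treat the within-group paired tests as descriptive.

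Cost: a wording change to both the acquisition and the analysis sections. Fixing the voxel position is an acquisition rule, so it has to reach the scanning staff as well as the analyst. The planned baseline and week-12 scans suffice and none are added.

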# 5 Adverse event

Serious Adverse Events are defined here as:

1. **Serious Adverse Events** – those which are fatal, life threatening, disabling or require hospitalisation or prolongation of hospitalisation. All deaths whether thought to be related to the trial intervention or not should be reported as serious adverse events.

1. **Unexpected Adverse Events** – those that would not be expected among elderly patients with AD (See known side effects in BNF).

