## **3.3 Intervention**

The TCM formula in our study was YHD, including Yinyanghuo (Epimedium) 10g, Nvzhenzi(Fructus ligustri lucidi) 10g, Buguzhi (Psoralea fruit) 10g, Heshouwu (Radix polygoni multiflori)10g, Huangqi (Radix astragali) 10g, Chuanxiong(Ligusticum wallichi franchat) 6g, Shichangpu(Acorus gramineus) 6g in one unit. Each herb was provided as herbal concentrate-granules in one bag and quality controlled by the Shenzhen Sanjiu Modern Chinese Medicine limited Company (Tianjin, China). Every patient in YHD group orally took 100 ml of the decoction once a day half hour after breakfast and DH-simulation 5 mg before sleep for 24 weeks. Patients in DH group orally took DH 5 mg a day before sleep provided by Eisai China Inc. (Tianjin, China), and YHD-simulation 100 ml of the decoction half hour after breakfast for 24 weeks.

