## **5.1 recording and reporting**

Care will be taken not to introduce bias when detecting AEs and/or SAEs. Open-ended and non-leading verbal questioning of the subject is the preferred method to inquire about AE occurrence. Regardless the relevance to the medicine, A it is the responsibility of the investigator to review all documentation (e.g., hospital progress notes, laboratory, and diagnostics reports) relative to the event. The investigator will then record all relevant information regarding an AE/SAE in the appropriate data collection tool.

The investigator will attempt to establish a diagnosis of the event based on signs, symptoms, and/or other clinical information. In such cases, the diagnosis will be documented as the AE/SAE and not the individual signs/symptoms.

If any patient suffers an event that fulfils these criteria, a Serious Adverse Event Form should be completed and faxed to the Principal Investigator **within 24 hours of the event being known.** The original form should be stored in the Investigator File and a copy placed in the patient’s source notes.

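### Unexpected events are listed inside the definition of a serious adverse event, and the 24-hour form is tied to that list without saying which item triggers it

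*Protocol*

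**What the plan says.** Section 5 (Adverse event) opens with the lead-in "Serious Adverse Events are defined here as" and places two numbered items under it.

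- The first item repeats the label for serious events and defines them by outcome: "those which are fatal, life threatening, disabling or require hospitalisation or prolongation of hospitalisation". It adds a sentence on deaths: "All deaths whether thought to be related to the trial intervention or not should be reported as serious adverse events".
- The second item is labelled as unexpected adverse events and defines them as "those that would not be expected among elderly patients with AD (See known side effects in BNF"). It sets no level of severity.

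Section 5.1 (recording and reporting) gives the operational rule: "If any patient suffers an event that fulfils these criteria, a Serious Adverse Event Form should be completed and faxed to the Principal Investigator", with the time limit "within 24 hours of the event being known". It does not say which of the two items the criteria are.

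Section 5.2 covers follow-up of all adverse events, serious or not, and does not return to the definition. No other section separates seriousness from expectedness.

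**The concern.** Seriousness and expectedness are different attributes of an event. Seriousness describes the outcome. Expectedness describes whether the event is already known, either for a product or for a population. Section 5 puts both under one definition, and Section 5.1 makes that definition the trigger for expedited reporting. An investigator who follows the text word for word will send an SAE form for a harmless event merely because it is unusual in this population.

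Two things are at stake. First, the SAE count from the trial may include events that are not serious. Second, three centres apply the rule (Section 3.2 gives 40, 20 and 60 patients, 120 in all). If they resolve the wording differently, the pooled count mixes definitions. An analysis plan could not fully repair this, because what goes on an SAE form is decided at the centre.

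The yardstick for expectedness is also unclear. Its main wording refers to what is usual in the patient population, and the bracket refers to a drug side-effect source. Where the two disagree, for example when a treatment-related event is also common in old age, the text does not say which prevails.

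**Working it through.** The documents give no SAE rate or expected count, so there is no figure to reproduce. The check is to set Sections 5 and 5.1 side by side and work through each way the two items can combine.

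Let S be the set of events that meet the outcome criteria of the first item, and U the set of events that meet the second item (unexpected). U has no severity threshold, so it can contain events outside S.

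1. **Either item suffices.** The lead-in governs both items, they are listed without a conjunction, and Section 5.1 refers to criteria in the plural. This is the literal reading. The SAE count is |S| + |U outside S|, which is at least |S|. No serious event is missed, but every non-serious unexpected event is added and gets a 24-hour form.

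2. **Only the first item triggers the form.** The two items are treated as two separate definitions under a careless lead-in, and the form's name ties it to the first. The count is |S|, which is correct. To get here a centre must set aside the lead-in, and nothing in Section 5.1 tells it to do so.

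3. **Both items are needed.** The count is |S and U| plus any death that was expected, because the sentence on deaths admits every death. This is at most |S|: a hospitalisation of a kind usual in this population would go unreported as an SAE. The reading is weak. There is no word joining the items, and a conjunctive test contradicts the sentence on deaths.

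The order is therefore: reading 3 ≤ reading 2 ≤ reading 1. The inflation under the literal reading equals the number of non-serious unexpected events. The protocol gives no basis for that number.

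On expectedness, Section 3.3 describes two active products: "Every patient in YHD group orally took 100 ml of the decoction once a day half hour after breakfast and DH-simulation 5 mg", against donepezil with a dummy of the decoction. The second item of Section 5 offers one population yardstick and one drug reference. It does not rank them, and the protocol names no safety reference for the seven-herb formula. This affects SAE counts only under readings 1 and 3, where the second item is part of the trigger.

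**The case against.** The strongest case on the other side is that this is untidy drafting and little more. The first item is a complete outcome-based definition under its own label, the second carries a different label, and the form is named for the first. Experienced investigators may well apply reading 2 and count correctly. The literal reading over-reports and misses no serious event. Section 5.1 has investigators record all relevant information on every adverse event, and Section 5.2 has every event followed, so a misclassified event could be found and reclassified. The trial is described as double-blind with 1:1 allocation, and nothing shows that differing readings would favour one arm. A reference for the formula may also exist outside the protocol.

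Most of this stands, and it limits the point. A reader might infer that SAE counts must be wrong however the text is read. They need not be: reading 2 gives the right count, and the reading that under-reports is the least plausible. A reader might also infer that expectedness ignores the study products altogether. The bracketed reference to a side-effect source contradicts that; the fault is two unranked yardsticks.

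What does not fall away is that the literal text makes non-serious unexpected events SAEs, and no other section corrects it. Relying on investigators to disregard the lead-in is no substitute for a clear rule.

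**Conclusion.** The point holds in limited form. As written, Sections 5 and 5.1 classify non-serious unexpected events as SAEs and call for 24-hour reporting of them. They also leave room for the three centres to count differently. The direction under the literal reading is inflation. The size cannot be given, because it depends on how many non-serious unexpected events occur and how each centre reads the list.

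The conclusion assumes that at least one centre applies the list literally, or that centres differ. If all apply the outcome criteria alone, the counts are sound and only the expectedness yardstick remains unclear.

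A reader might also take SAEs to be the trial's main safety comparison. The protocol does not say so: the safety outcomes listed in Section 4.1.1 are routine blood, urine and stool tests, the electrocardiogram, and liver and kidney function. The defect is in an operational definition. It is worth correcting but does not invalidate the trial.

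**What to change.** Reconcile Sections 5 and 5.1 as follows.

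- Define an SAE solely by the outcome criteria already in the first item of Section 5, keeping the sentence on deaths.
- Move unexpected events out from under the SAE lead-in and give them their own definition.
- In Section 5.1, replace the general reference to criteria with a statement that the outcome criteria alone trigger the SAE form and the 24-hour report, whether or not the event is expected.
- Record expectedness as a separate field, judged against a named safety reference for each study product, the formula and donepezil. If a reference for the formula already exists elsewhere, cite it.

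The cost is a few lines of text and one added field on the case report form. Patients undergo no extra procedure, and the protocol's own seriousness criteria do not change. Non-serious unexpected events stay on record as adverse events under Section 5.1. A centre that had required both items would report some serious but expected events that it would otherwise have left out.
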